**ORGANS AT RISK**	
Brain stem	Dmax < 23,1Gy V18Gy < 0,5 cc
Optic chiasm	Dmax< 17,4Gy
Optic nerves	Dmax<15Gy
Spinal cord	Dmax<15Gy
Healthy brain (cranial cavity – GTV)	V23,1Gy < 7 cc
	V18Gy < 20 cc

*Irradiation technique*

All treatment will be performed on LINAC, 6 MV X-ray photons, up to 1400 UM/min. The SRT mode is left open to the participating institutions depending on their equipment.

Doses delivered to target volumes (Dmin, 98, 2%, max GTV, Dmin, 98, 2%, max PTV, % PTV coverage by isodose 70%), to organs at risk (Dmax and D2% for at-risk organs and VxGy for healthy brain) and the quality indicators (Paddick’s conformity index and gradient index) will be recorded.

*Treatment verification and accuracy*

An online review of the optimal patient repositioning system will be systematically performed before each fraction according to each centre’s policy and equipment. Any necessary offset correction will be applied.

*Treatment interruptions / changes*

No changes (major deviations) will be permitted with regard to the target volume selection and delineation, the radiation dose prescriptions or the overall treatment duration. Local investigators will carefully follow their patients during treatment and take all adequate measures to avoid any interruption and/or change in the total dose. It is, however, the local investigator’s responsibility to interrupt treatment delivery if deemed appropriate in the patient’s best interest. Any such interruptions will be recorded in the electronic case report form (eCRF). In case of machine breakdown or a non-working day, all due measures will be taken to avoid prolonging the overall treatment duration.

*Time lapse between SRT and surgery*

Complete removal of the metastasis will be carried out by the neurosurgeon within ≤3 days from the end of the SRT. Postoperative imagery will be performed within 48 h following surgery.

### Study procedures and participant timeline

An overview of the study assessments and procedures is presented in Table 3.

**Table 3 Tab3:** Data collection schedule

				Follow-up			
	**Inclusion**	**Preop SRS**	**Surgery**	M3	M6	M9	M12
Consent	**✓**						
Medical and surgical history	**✓**						
History of the disease	**✓**						
DS GPA classification	**✓**						
Serum Pregnancy Test (for woman of childbearing age)	**✓**						
Clinical examination	**✓**	**✓**		**✓**	**✓**	**✓**	**✓**
Previous and concomitant treatment	**✓**	**✓**		**✓**	**✓**	**✓**	**✓**
Toxicity Evaluation (NCI CTCAE v5.0)		**✓**	**✓**	**✓**	**✓**	**✓**	**✓**
MMSE and EORTC QLQ-C30 questionnaires	**✓**			**✓**	**✓**	**✓**	**✓**
Surgery information (date, quality of surgery and post-operative follow-up)			**✓**				
Dosimetric brain MRI	**✓**						
Dosimetric CT scan	**✓**						
Tumor sample (FFPE block)	**✓**						
Dose delivered to target volumes and organs at risk		**✓**					
Paddick conformity Index and Gradient Index		**✓**					
Brain MRI			**✓**^a^	**✓**	**✓**	**✓**	**✓**

^a^ within 48 h postoperatively (scanner accepted if MRI is not available)

Seven consultations are planned for each enrolled patient: inclusion, preoperative SRT, brain metastasis surgery within the 3 following days, and follow-up every three months (M3, M6, M9, M12). The study layout is presented in Fig. 1.

**Fig. 1 Fig1:**
[figure not shown]
Scheme of the STEP study

### Statistical analysis

#### Sample size

For sample size calculation, two elements have been taken into account: the primary objective of efficacy at 6 months and the secondary endpoint of 1-year radio-necrosis toxicity.

The efficacy of pre-operative SRT is expected to be at least equivalent to postoperative SRT, estimated at 70%. The experimental plan of the study is Fleming’s one-stage design with a sufficient efficacy threshold set at 86% (higher than rates observed in retrospective studies) and an insufficient efficacy threshold set at 70%. In order to control the (one-sided) type I error rate α at 5% and type II error rate β at 10%, the minimum number of patients to be enrolled should be 57.

For the incidence of radio-necrosis at 1 year, to conclude to a decrease compared to that induced in the case of postoperative SRT, a percentage lower than 5% (as observed in the retrospective series) will be accepted and we decided to reject proportions exceeding 15%. To ensure α < 5% and β < 20%, it is sufficient to include 59 patients. The less restrictive hypothesis in terms of power in this second Fleming’s design was decided on the basis that it concerns a secondary objective.

Thus, by including 70 patients, it is possible to compensate for a proportion of more than 15% missing data (for whatever reason) and hence to ensure adequate power of the study in terms of main objective and first secondary objective (the evaluation of the incidence of radio-necrosis).

The treatment will be considered efficacious (and therefore the trial positive) if at least 56/70 of the patients achieve local control. In this case, the estimate of the probability of success will be 80% (90% confidence interval of 71.3–86.9%, Jeffreys method), at least. The treatment will be considered to induce an acceptable level of radio-necrosis if no more than 5/70 patients have this toxicity, and, in this case, the estimate of the probability of toxicity will be 7% (90% confidence interval 3.3–13.6%, Jeffreys method), at least.

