## Methods/design

### Study design

STEP has been designed as a national, multicentre, open-label, prospective, non-randomized, phase-II trial to evaluate the efficacy and toxicity of preoperative SRT for patients with brain metastases.

The experimental plan will be run using Fleming’s single-stage design without interim evaluation.

This study has been registered on Clinicaltrials.gov (NCT04503772). Seventy patients are expected to be enrolled. The study was started in February 2021 with an 18-month enrolment period and an estimated completion date by July 2023.

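### Radio-necrosis power does not hold across the missing-data allowance: with 63 to 67 of 70 patients assessable, no cut-off gives both α < 5% and β < 20%

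*Protocol article*

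**What the plan says.** The protocol article describes a Fleming "single-stage design without interim evaluation" (Study design). The Sample size section sizes it for two endpoints.

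- **Six-month local control (primary):** 70% is insufficient and 86% sufficient. The aim is to "control the (one-sided) type I error rate α at 5% and type II error rate β at 10"%, and "the minimum number of patients to be enrolled should be 57".
- **One-year radio-necrosis (first secondary objective):** 5% is acceptable and 15% is to be rejected. "To ensure α < 5% and β < 20%, it is sufficient to include 59 patients".

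It then draws a conclusion from the two numbers: "by including 70 patients, it is possible to compensate for a proportion of more than 15% missing data (for whatever reason"). From this it infers that power is adequate for both objectives. Cut-offs are given for the full 70 only: at least 56 with local control, and at most 5 with radio-necrosis.

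Three later passages say how missing patients are treated. Primary analysis provides a Kaplan-Meier estimate, set against an adjusted rejection rate, for patients who cannot be assessed for local control. Secondary analyses reports toxicities as percentages with confidence intervals. Missing data says that missing values are not replaced but dropped.

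**The concern.** The step from 59 being sufficient to 70 being enough after losses assumes that any number between 59 and 70 does at least as well as 59. With a whole-number cut-off this is not so. While the cut-off stays fixed and patients are added, the chance of passing falls under both the good and the bad rate. So α and power both decline until α leaves room to raise the cut-off by one, when both jump. Between jumps, power can sink below its target although there are more patients.

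At stake is the conclusion on radio-necrosis, the safety argument for preoperative SRT. If a few patients are not assessable at one year, the team may have to choose between a rule that misses the power target and one that exceeds the α limit. If the rule is not fixed beforehand, that choice could be made with the count already known.

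**Working it through.** **Inputs (protocol article, Sample size).** Radio-necrosis: unacceptable rate 0.15, acceptable rate 0.05, α < 5%, β < 20%. Efficacy: 0.70 against 0.86, one-sided α 5%, β 10%. Enrolment 70.

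**Formulas.** With n assessable and X binomial:
- Radio-necrosis, accept if X ≤ c: α = P(X ≤ c | n, 0.15); power = P(X ≤ c | n, 0.05).
- Efficacy, positive if X ≥ r: α = P(X ≥ r | n, 0.70); power = P(X ≥ r | n, 0.86).

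**Step 1: the plan's own figures are reproduced.**
- Efficacy, n = 57, r = 46: α 4.86%, power 90.6%. This is the smallest n that meets both limits.
- Radio-necrosis, n = 59, c = 4: α 4.69%, power 82.8%. This is also the smallest n (at 58, c = 4 has α 5.19%, and c = 3 has power 67.0%).
- Inflation: 59 / 0.85 = 69.4, so 70. Losing 11 of 70 is 15.7%, which matches the stated allowance.
- At full enrolment, ≥56/70 has α 4.13% and power 94.1%; ≤5/70 has α 3.84% and power 86.3%.

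**Step 2: radio-necrosis at each number from 59 to 70.**

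| Assessable | Missing of 70 | ≤4: α | ≤4: power | ≤5: α | ≤5: power | Both limits met? |
|---|---|---|---|---|---|---|
| 59 | 15.7% | 4.7% | 82.8% | 10.6% | 92.6% | yes, ≤4 |
| 60 | 14.3% | 4.2% | 82.0% | 9.7% | 92.1% | yes, ≤4 |
| 61 | 12.9% | 3.8% | 81.1% | 8.9% | 91.6% | yes, ≤4 |
| 62 | 11.4% | 3.4% | 80.2% | 8.1% | 91.1% | yes, ≤4 |
| 63 | 10.0% | 3.1% | 79.3% | 7.4% | 90.5% | no |
| 64 | 8.6% | 2.8% | 78.4% | 6.8% | 90.0% | no |
| 65 | 7.1% | 2.5% | 77.5% | 6.2% | 89.4% | no |
| 66 | 5.7% | 2.3% | 76.6% | 5.6% | 88.8% | no |
| 67 | 4.3% | 2.0% | 75.7% | 5.1% | 88.2% | no |
| 68 | 2.9% | 1.8% | 74.7% | 4.7% | 87.6% | yes, ≤5 |
| 69 | 1.4% | 1.6% | 73.8% | 4.2% | 86.9% | yes, ≤5 |
| 70 | 0% | 1.5% | 72.8% | 3.8% | 86.3% | yes, ≤5 |

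A cut-off below 4 lowers power further and one above 5 raises α further, so at 63 to 67 nothing else works. The largest shortfall is 80 − 75.7 = 4.3 points, at 67 assessable, a loss of only three patients.

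**Step 3: can the stated 5/70 be carried over?**
- Keeping ≤5 at 59 assessable gives α 10.6%, about twice the limit.
- Scaling the proportion gives 5 × 68/70 = 4.86 and 5 × 69/70 = 4.93, which permit only 4 events. Power is then 74.7% or 73.8%, although ≤5 would have met both limits.

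**Step 4: efficacy, for comparison.** Assume that non-assessable patients leave the denominator and that the smallest r with α ≤ 5% is used:
- n = 59, r = 48: α 3.5%, power 88.5%.
- n = 60, r = 49: α 3.0%, power 87.4%.
- n = 64, r = 52: α 3.0%, power 89.5%.
- n = 61–63 and 65–70: power 90.5% to 94.7%.

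Lowering r by one at 59, 60 or 64 would give α of 6.6%, 5.7% or 5.6%.

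**The case against.** The case against has several parts, and much of it stands.

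- **No printed number is wrong.** This stands. 57 and 59 are true minima, and both rules at 70 meet their targets comfortably.
- **The text promises adequate power, not 90% or 80% at every residual number.** This stands in part. The shortfalls are small and α can be kept under 5% throughout. But the only benchmarks given are β 10% and β < 20%, and adequacy is presented as following from 57 and 59, so it is naturally read against them.
- **For the primary endpoint, the count rule is not the planned analysis when patients are missing.** This stands. The Kaplan-Meier fallback uses partial follow-up, so the efficacy figures in Step 4 are only indicative. The fallback does not extend to radio-necrosis. There, percentages and the dropping of missing values lead to the reduced denominator used in Step 2.
- **A table of cut-offs belongs in the SAP.** It may well be there, and its absence from an article is not the complaint. The complaint is the property that the article asserts over a range of losses.

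A reader might go further and infer that 57 and 59 are both isolated values that happen to work, so that the missing-data claim is simply false at 59 assessable. The documents do not support that. For radio-necrosis, 59 begins a run to 62 in which both limits are met. Only the efficacy number has failing neighbours on both sides, and the efficacy gap at 59 is 1.5 points, due to discreteness, with just 3.5% of the 5% α used.

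**Conclusion.** The concern holds as a minor one and rests mainly on radio-necrosis. At 63 to 67 assessable patients, inside the stated allowance, the plan's own limits cannot both be met: power is 79.3% down to 75.7% with α controlled, or α is 7.4% down to 5.1% with the looser cut-off. At 59 to 62 and 68 to 70 the design works as stated. Efficacy power falls at most 2.6 points short (87.4% at 60), under a count rule that the plan may not apply.

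The result assumes exact binomial tails, the planning rates of 5% and 15%, removal of patients without a one-year radio-necrosis assessment from the denominator, and a lower end of the allowance at 59, the plan's own requirement. It implies neither that 70 is too few nor that the rules at 70 are wrong.

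**What to change.** In Sample size, replace the general assurance of adequate power with the figures: with 59 to 70 assessable, exact power is about 76–88% for radio-necrosis and, under the count rule, about 87–95% for efficacy.

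Prespecify the radio-necrosis cut-off by number assessable, with its exact α and power, before the one-year data are seen:
- ≤4 for 59 to 67 assessable (α 4.7% to 2.0%, power 82.8% to 75.7%);
- ≤5 for 68 to 70 assessable (α 4.7% to 3.8%, power 87.6% to 86.3%).

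If the SAP already holds such a table, a reference to it and the corrected power range are enough.

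The cost is a sentence, a short table and a slightly less favourable stated power. Enrolment and the rules at 70 stay as they are.

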To date, four prospective studies on postoperative SRT have been published and have shown an estimated local control rate of 70% at 6 months and 62% at one year, with an increased risk of radio-necrosis (nearly 18% at one year) and leptomeningeal relapse (nearly 17% at one year) [9, 12–14]. A phase-III randomized study conducted on 194 patients compared WBRT to postoperative SRT [9]. With a median follow-up of 11 months, the authors showed that the survival time without cognitive deterioration was longer for patients treated with postoperative SRT than for those treated with WBRT (respectively, a median of 3.7 months [CI95 3,45-5,06] vs. 3.0 months [CI95 2,85-3,25]; HR 0,47 [CI95 0,35-0,63]; *p* < 0.0001). Furthermore, six-month cognitive deterioration was significantly less frequent for patients treated with postoperative SRT (− 33.6% [CI95–45,3-21,8]; *p* < 0.00031). No differences were found between the groups in terms of overall survival (HR 1,07; [CI95 0,76-1,50]; *p* = 0.7). However, postoperative SRT has several drawbacks: difficulties in delineating the target volume, a high volume of irradiation, a high rate of leptomeningeal recurrence and long overall treatment time (3–6 weeks between surgery and SRT). The alternative to postoperative SRT could be preoperative SRT, providing local control remains at least equivalent. This is an innovative concept that could enable the benefits of SRT to be retained with fewer drawbacks than with postoperative SRT.

To date, three retrospective series of preoperative SRT with a limited number of patients have been published and seem to confirm these advantages [15–17]. The median dose prescribed was 14 Gy (1 fraction) on isodose 80% without any margin around the metastasis. Surgery was most often carried out within 24–48 h following SRT.

A retrospective study conducted by Asher et al. on 47 patients treated with preoperative SRT showed 6-month and 12-month survival rates of 77,8 and 60% respectively [15]. The six-month local control rate was 97,8%, falling to 85,6% and 71,8% at 12 and 24 months respectively. With 12 months’ hindsight, no radio-necrosis or leptomeningeal relapse was found in the cohort.

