##### Assessment of the radio-necrosis incidence at 1 year

Radio-necrosis is histologically defined post-operatively, either according to the anatomo-pathological report, or in the absence of salvage surgery, by the appearance of or increase in gadolinium contrast on T1 MRI sequences, associated with an increase in the cerebral blood volume (CBV) ratio (brain blood volume of the tumour / brain blood volume of the non-tumoural white matter) of under 2 on perfusion MRI sequences and/or a standard uptake volume (SUV max) of less than 1.59 on PET scanner at F-DOPA. It will be evaluated at the M12 follow-up visit on cerebral MRI.

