#### Participant eligibility

The inclusion and non-inclusion criteria are presented in Table 1. Patients will be eligible for the study if they have no more than 4 distinct brain metastases, including one with a surgical indication, an indication for SRT and surgery, and no contraindication for MRI. They will be ineligible if they have metastases from sarcoma or small-cell lung cancer, if they have a documented leptomeningeal disease, or if their survival is estimated under 6 months according to the DS GPA (diagnosis-specific graded prognostic assessment).

**Table 1 Tab1:** Selection criteria

Inclusion criteria	Non-inclusion criteria
≤ 4 distinct brain metastases, one with surgical indication	Lymphoma, leukaemia, multiple myeloma, germinal tumours or cerebral primary cancer
Diagnosis of histologically proven breast, digestive, non-small cells lung cancer, kidney or melanoma	Metastases from small-cells lung cancer or sarcoma
≤ 5 cm larger diameter	Mass effect with deflection ≥5 mm from median line or hydrocephaly or compression 4th ventricle, patient neurologically unstable, need for emergency decompressive surgery
Karnofsky performance status ≥70	> 4 brain metastases
No contraindication for MRI	Contraindication to anaesthesia, MRI or gadolinium injection
Possibility for the patient to be treat with both surgery and stereotactic radiotherapy	Proximity of the tumour with organs at risk which do not allow the prescribed dose to be reached in the envelope
≥ 18 years old	Pregnant or breastfeeding woman
Estimated overall survival ≥6 months according to DS GPA	Anti VEGF within 6 weeks before treatment
Written inform consent signed	Documented leptomeningeal injury
Affiliation to the French social security system	History of irradiation of the encephalon in toto
For women of childbearing age including those on LH-RH agonists for ovarian suppression: inclusion negative serum pregnancy test (≤ 7 days prior to the start of preoperative RSH).	History of stereotactic radiotherapy on metastasis to be operated on
	Non-candidate patient for surgery
	Surgical delay > 3 days compared to stereotactic radiotherapy
	Estimated survival < 6 months by DS GPA
	Patient under guardianship or curatorship
	Psychological disorder (cognitive disorders, mental alertness, etc.) or social (deprivation of liberty by judicial or administrative decision) or geographical reasons that may compromise medical monitoring of the trial or compliance with treatment

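### The radio-necrosis cut-off of 5/70 is not adjusted for patients not assessable at M12, and misses its stated 5% error rate at the plan's own missing-data allowance

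*Protocol article*

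**What the plan says.** All places are in the protocol article.

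- **Sample size**, hypotheses: "a percentage lower than 5% (as observed in the retrospective series) will be accepted and we decided to reject proportions exceeding 15"%. Size: "To ensure α < 5% and β < 20%, it is sufficient to include 59 patients".
- **Sample size**, allowance: "by including 70 patients, it is possible to compensate for a proportion of more than 15% missing data (for whatever reason").
- **Sample size**, decision rule: "The treatment will be considered to induce an acceptable level of radio-necrosis if no more than 5/70 patients have this toxicity". The resulting estimate is given as 7%, with a 90% Jeffreys interval of 3.3–13.6%, and is described as a minimum.
- **Assessment of the radio-necrosis incidence at 1 year**: the diagnosis is made "either according to the anatomo-pathological report, or in the absence of salvage surgery, by the appearance of or increase in gadolinium contrast" with further imaging criteria. On timing: "It will be evaluated at the M12 follow-up visit on cerebral MRI".
- **Primary analysis**: for non-assessable patients, a Kaplan-Meier estimate and an adjusted rejection rate are planned, for local control only.
- **Secondary analyses**: toxicities are analysed as percentages with confidence intervals.
- **Missing data**: values are not replaced, and cases are dropped by partial elimination. Imputation remains possible if relevant.
- **Table 3**: brain MRI is scheduled at M3, M6, M9 and M12.
- **Background**: the 47-patient retrospective preoperative series "showed 6-month and 12-month survival rates of 77,8 and 60% respectively". **Table 1** requires "Estimated overall survival ≥6 months according to DS GPA".

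**The concern.** For a toxicity rule with an upper cut-off, a patient who cannot contribute an event moves the result towards acceptance. The sample was raised from 59 to 70 to absorb missing outcomes, but the cut-off was then set as if all 70 would be observed. Partial elimination would shrink the denominator, whereas the rule fixes it at 70. The two sections do not fit together.

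The plan recognises this problem for local control and adjusts for it there to protect the alpha risk. It offers no counterpart for radio-necrosis, which is named as the first secondary objective, helped to set the sample size, and is one of the advantages claimed over postoperative SRT in the Discussion. At stake is a conclusion of acceptable toxicity that owes something to early death or loss to follow-up rather than to the treatment.

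**Working it through.** **Inputs.** Acceptable rate 5%, unacceptable rate 15%, α < 5%, β < 20%, 59 patients, rule of at most 5 of 70, and a missing-data allowance just over 15% (all from Sample size). Survival at 12 months is assumed to be 60%, 70% or 80%. The article states no such figure for this trial; 60% is its only preoperative 12-month figure.

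**Step 1: reproduce the plan.** For n patients, take the largest c with P(X ≤ c | n, 0.15) ≤ 0.05. Power is then P(X ≤ c | n, 0.05), exact binomial.

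- n = 59: c = 4, α = 0.047, power = 0.828. Scanning n upward from 40, this is the first n that meets both limits, so 59 is confirmed.
- n = 70: c = 5, α = 0.038, power = 0.863. The rule is sound with complete data.
- Jeffreys 90% interval for 5/70, from Beta(5.5, 65.5): 3.3–13.5%. The article prints 13.6%.

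**Step 2: keep the cut-off at 5 and reduce the number assessable.** P(X ≤ 5 | n, 0.15):

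| Assessable | Probability of accepting a 15% rate |
|---|---|
| 70 | 0.038 |
| 68 | 0.047 |
| 67 | 0.051 |
| 60 | 0.097 |
| 59 | 0.106 |

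The stated limit fails once more than two patients are not assessable. The plan's own allowance gives 70 × 0.85 = 59.5, about 59 patients, where the error is more than twice the limit. This step uses no survival assumption.

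**Step 3: deaths, if only M12 findings count.** Assessable = 70 × survival, with 5 still the cut-off:

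- 80%: n = 56, probability 0.136
- 70%: n = 49, probability 0.236
- 60%: n = 42, probability 0.383

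**Step 4: deaths, if necrosis before death is recorded.** Assume constant hazards, a 15% necrosis risk at 12 months in the absence of death, and detection as it occurs. Over one year h = −ln(0.85) = 0.1625 and d = −ln(survival). The observable incidence is h/(h+d) × (1 − e^−(h+d)), and acceptance is P(X ≤ 5 | 70, incidence):

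- 80%: incidence 13.5%, probability 0.08
- 70%: incidence 12.7%, probability 0.11
- 60%: incidence 11.8%, probability 0.15

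If all necrosis arose between M6 and M12, with the retrospective series' survival of 77.8% at 6 months and 60% at 12 months, the incidence is 10.3% and the probability 0.26.

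**Step 5: cut-offs that keep α ≤ 5%.** 5 for 68–70 assessable, 4 for 59–67, 3 for 50–58, 2 for 40–49. Power at a 5% rate is 0.83 at 4/59, 0.76 at 3/50 and 0.65 at 2/42.

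**The case against.** A reader might infer that the plan counts patients who die before M12 as free of necrosis, and that the error therefore rises from 4% to 38%. The documents do not support that as a statement of fact. No section says how such deaths are counted, and partial elimination points the other way. The 38% also needs two things together: 60% survival, taken from a 47-patient retrospective series, and no necrosis recorded in anyone who dies. This trial selects patients on estimated survival and performance status, schedules MRI at M3, M6 and M9, and accepts a pathology report.

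The limits may also be meant as a crude cumulative incidence with death as a competing event. A patient who dies without necrosis is then properly a non-event, the denominator is 70, and α stays at 0.038, provided necrosis before death is counted. That is a legitimate choice, so the plan should not be made to censor deaths in a Kaplan-Meier analysis.

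Finally, this is a secondary endpoint with deliberately relaxed power, it does not decide whether the trial is positive, and an SAP that is not shown may deal with deaths.

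All of this stands, and it limits the size and weight of the point. It does not rescue the cut-off. The rule and its error rate are fixed in the article itself, and they disagree at the article's own missing-data allowance. The competing-event reading does not help with patients who are lost or unscanned, and placing the evaluation at M12 does not secure the recording of earlier necrosis.

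**Conclusion.** Wrong as written; should be fixed, as a secondary-endpoint matter. The firmest result needs no outside assumption: a cut-off of 5 meets α < 5% only with at least 68 assessable patients and gives 0.106 at 59.

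The effect of deaths is less certain. Over assumed 12-month survival of 60–80%, the chance of accepting a 15% rate is about 0.08–0.15 if necrosis before death is recorded (constant hazards) and 0.14–0.38 if only M12 findings count. The value 0.38 is the worst case and not an expected value. Both ranges take the 15% limit as risk in the absence of death; under a crude incidence with complete recording, the error remains 0.038. That deaths count as necrosis-free is an implication of a fixed denominator with M12 evaluation, not something the article states.

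Two small slips sit in the same sentence. A rule of no more than 5/70 gives an estimate of at most 7% (5/70 = 7.1%), not at least. The Jeffreys upper limit is 13.5% rather than 13.6%, which changes nothing.

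**What to change.** 1. Count radio-necrosis found on any scheduled MRI (M3, M6, M9, M12) or on histology up to M12.
2. State whether the 5% and 15% limits refer to cumulative incidence with death as a competing event (denominator 70) or to the rate among assessable patients.
3. For patients lost or unscanned, or throughout if the assessable rate is meant, tie the cut-off to the number assessable: at most 5 for 68–70, 4 at 59, 3 at 50, 2 at 42. Alternatively, accept only if the upper one-sided 95% limit of the 12-month incidence is below 15%.
4. Bring the Missing data section into line with whichever choice is made.
5. Correct the direction of the 7% statement and the 13.6%.

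The cost is wording only, since the MRIs are already scheduled. The downside is that the power that can be stated falls with fewer assessable patients: 0.83 at 59, 0.76 at 50 and 0.65 at 42. Because the cut-off moves in whole steps, power also dips below 0.80 just short of each step, for example 0.76 at 67 assessable with a cut-off of 4.
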